#### **8.1.2 Secondary endpoints:**

- Assessment of treatment satisfaction of HIV+ patients who start monotherapy with LPV/r tablets versus triple therapy containing any PI using the CESTA questionnaire (Spanish Questionnaire of Satisfaction with Antiretroviral Treatment) [21] from the baseline visit to study week 24.
- Assessment of treatment adherence by HIV+ patients who start monotherapy with LPV/r tablets versus triple therapy containing any PI using the GEEMA questionnaire [22] and a visual analog scale (VAS) [23].
- Assessment of regimen tolerability and safety in HIV+ patients who start monotherapy with LPV/r tablets versus triple therapy containing any PI.
- Proportion of patients with a viral load <50 copies/mL of HIV RNA at 24 weeks in HIV+ patients who start monotherapy with LPV/r tablets versus triple therapy containing any PI. A viral load >500 copies/mL of viral RNA (HIV-1) confirmed at study week 24 will be considered as virological failure.
- Changes in immune response in HIV+ patients who start monotherapy with LPV/r tablets versus triple therapy containing any PI, as measured through the change in CD4+ cell count from the baseline visit to study week 24

## 8.2. STUDY CONDUCT

### 8.2.1 Study timetable and procedures.

Procedures are shown in the following table and detailed below:

|                                              | Screening visit | Baseline visit  | Week 4 visit | Week 12 visit | Week 24 visit | Early discontinuation visit |
|----------------------------------------------|-----------------|-----------------|--------------|---------------|---------------|-----------------------------|
| Randomization                                |                 | X (24 h before) |              |               |               |                             |
| Informed consent                             | X               | X               |              |               |               |                             |
| Clinical history                             | X               | X               |              |               |               |                             |
| Complete physical examination  | X               | X               |              | X             | X             | X                           |
| Pregnancy test                 | X               | X               |              |               |               |                             |
| HIV-1 RNA in plasma                          | X               | X               | X*           | X             | X             | X                           |
| CD4 count                                    | X               | X               | X*           | X             | X             | X                           |
| Hepatology**                                 |                 | X               |              | X             | X             | X                           |
| Chemistry (2)**                   |                 | X               |              | X             | X             | X                           |
| MOS-HIV Questionnaire                 |                 | X               |              |               | X             | X                           |
| EQ-5D Questionnaire                   |                 | X               |              |               | X             | X                           |
| CESTA Questionnaire                          |                 | X               | X*           | X             | X             | X                           |
| GEEMA Questionnaire                          |                 | X               | X*           | X             | X             | X                           |
| Adherence VAS                                |                 | X               | X*           | X             | X             | x                           |
| Concomitant medication                       |                 | X               | X*           | X             | X             | X                           |
| Adverse events                               |                 | X               | X*           | X             | X             | X                           |

(1) includes vital signs and weight measurement. Since adult patients will be enrolled, height will be measured at the baseline visit.

\*Only for patients in the experimental arm.

\*\*Record relevant data related to adverse events.

(2) Urine pregnancy test for women of childbearing age.

Any deviation from the protocol procedures should be reported to the sponsor and recorded in the Case Report Forms (CRFs).

All laboratory samples will be sent to local laboratories to be tested. The same local laboratory should be used throughout patient participation in the trial.

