### **7.2 Patient withdrawal criteria**

#### **Therapeutic failure**

Patients who meet therapeutic failure criteria will be withdrawn from the study. These criteria are defined as follows:

1. In patients receiving triple therapy randomly assigned at baseline, documented virological failure, i.e. the presence of a viral load greater than 500 copies/mL on 2 occasions 15 days apart, is considered as therapeutic failure.
2. Patients assigned to maintenance with LPV/r alone who reach the virological failure criterion will be considered as therapeutic failures if protease gene mutations exist, so that the patient cannot be reinduced with nucleosides and would discontinue the study because of the need of a therapy not based on LPV/r.
3. However, patients assigned to maintenance with LPV/r alone can be reinduced with the same nucleosides as withdrawn if no documented resistance to LPV/r exists. Thus, the following specific situation (a+b+c) will NOT be considered as therapeutic failure and will not lead to study discontinuation:
  - a) A patient in the maintenance arm with LPV/r alone has a viral load greater than 500 copies/mL on 2 occasions 15 days apart.
  - b) The genotypic resistance test shows no resistance to LPV/r.
  - c) The patient is reinduced with the same nucleosides as received before study entry and completes the follow-up period with an undetectable VL.

If this situation has occurred, and once patients are reinduced, they will be considered as therapeutic failures when the following conditions are met:

- 4 weeks after reinduction, viral load has not decreased by at least one decimal logarithmic unit
- and/or does not become undetectable again (<50 copies/mL) at 16 weeks of reinduction
- or if once on triple therapy they experience virological failure again.

In patients in whom a viral load ranging from 50-500 copies/mL is obtained, the above procedure will be followed.

After this viral load has been confirmed three times (2 weeks, 2 weeks, and 4 weeks), the following will be done:

- Patients in the monotherapy group and with no lopinavir resistance will be reinduced with the same nucleosides and the procedure in the previous paragraphs will be followed.
- Patients on triple therapy or in the monotherapy group but with lopinavir resistance: these will be considered as therapeutic failures, and after designing rescue treatment a follow-up visit will be scheduled 4 weeks after the end of study visit.

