### **Baseline visit:**

If laboratory data for confirming screening criteria have been obtained within two months of study recruitment and are available, the screening visit may be the same as the baseline visit.

The study drugs should start to be taken within 24 hours of the baseline visit. The following assessments should be available at the baseline visit:

- Physical examination (vital signs, height and weight).
- Quality of life questionnaires (MOS-HIV and EQ-5D)
- A negative urine pregnancy test for women of childbearing age.

- Complete blood count (red blood cell count, white blood cell count and differential, and platelet count).
- Fasting chemistry profile (alkaline phosphatase, ALT, AST, GGT, total bilirubin, creatinine, glucose, potassium, sodium, uric acid, lipid profile (total cholesterol, HDL-C, LDL-C, VLDL-C, triglycerides).
- CD4 cell count
- HIV-1 RNA in plasma: This will be measured in real time at the site using the standard virological methods at each site. The same methods should be used throughout the study for each subject.
- CESTA questionnaire to assess satisfaction with antiretroviral treatment.
- GEEMA questionnaire to assess treatment adherence
- VAS to assess treatment adherence
- Recording of concomitant medication
- Adverse events

Once the baseline visit procedures and assessments are reviewed, subjects will be centrally randomized at the study data center after data are received.

Patients randomized to group B will return for HIV RNA monitoring at treatment week 4 (+/- 2 days)

The following assessments should be completed at the **week 12 and week 24 visits or at the study discontinuation visit**. Study visits should be scheduled to occur within  $\pm 1$  week of the date specified for weeks 12 and 24, calculating the dates from the baseline visit:

- Physical examination (vital signs, weight).
- Complete blood count (red blood cell count, white blood cell count and differential, and platelet count)
- Fasting chemistry profile (alkaline phosphatase, ALT, AST, GGT, total bilirubin, creatinine, glucose, potassium, sodium, uric acid, lipid profile (total cholesterol, HDL-C, LDL-C, VLDL-C, triglycerides)
- CD4 cell count
- HIV-1 RNA in plasma: If the patient shows at any time a detectable viral load (> 50 copies/mL), the test should be repeated within 2 weeks for confirmation. Annex 1 provides suggestions for management of these cases
- Concomitant medication
- Adverse events

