### **12.3. Secondary endpoints**

- Assessment of treatment satisfaction of HIV+ patients who start monotherapy with LPV/r tablets versus triple therapy containing any PI using the CESTA questionnaire (Spanish Questionnaire of Satisfaction with Antiretroviral Treatment) from the baseline visit to study week 24.

- Assessment of treatment adherence by HIV+ patients who start monotherapy with LPV/r tablets versus triple therapy containing any PI using the GEEMA questionnaires and a visual analog scale (VAS).
- Assessment of regimen tolerability and safety in HIV+ patients who start monotherapy with LPV/r tablets versus triple therapy containing any PI.
- Proportion of patients with a viral load <50 copies/mL of HIV RNA at 24 weeks in HIV+ patients who start monotherapy with LPV/r tablets versus triple therapy containing any PI. A viral load >500 copies/mL of viral RNA (HIV-1) confirmed at study week 24 will be considered as virological failure.
- Changes in immune response in HIV+ patients who start monotherapy with LPV/r tablets versus triple therapy containing any PI, as measured through the change in CD4+ cell count from the baseline visit to study week 24

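### Adverse events are asked about at week 4 in the monotherapy arm only, so early non-serious events are ascertained unequally between the arms

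*Protocol*

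**What the plan says.** The table in section 8.2.1 schedules adverse-event recording at baseline, week 4, week 12, week 24 and early discontinuation: "Adverse events | | X | X* | X | X | X". The week-4 entry is starred, and the star means "Only for patients in the experimental arm". The same star marks week-4 viral load, CD4, CESTA, GEEMA, the adherence scale and concomitant medication. The baseline-visit text in section 8.2.3 agrees: "Patients randomized to group B will return for HIV RNA monitoring at treatment week 4". No week-4 contact with group A appears anywhere in the protocol.

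Sections 8.1.2 and 12.3 list as a secondary endpoint "Assessment of regimen tolerability and safety in HIV+ patients who start monotherapy with LPV/r tablets versus triple therapy containing any PI". Section 9.1 says that all adverse events go into the CRF, but describes routine monitoring as serving to detect serious events. Serious events are reported continuously in both arms, from consent to 30 days after the last dose. The sample-size text in section 12 anticipates more diarrhoea in the experimental group on starting the new therapy.

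In Annex 3, one GEEMA item asks for the number of full days without medication since the preceding visit. Another GEEMA item covers the past week, and the adherence scale covers the past month.

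**The concern.** Non-serious adverse events come to light mainly when patients are asked. Group B is asked three times after baseline (weeks 4, 12 and 24) and group A twice (weeks 12 and 24). The extra question falls in the first weeks after a switch, when transient events such as diarrhoea are expected in B. In A, a mild event in weeks 0 to 4 must be remembered for at least eight weeks to be reported at a scheduled visit. In an open-label comparison, a true early excess in B then cannot be separated from the effect of asking B sooner. The distortion runs against monotherapy.

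The GEEMA item has a related fault in the other direction: at week 12 group A reports over a longer period and will show more missed days at the same true adherence.

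**Working it through.** The plan gives no figure on this point, so there is none to reproduce. The inputs are the visit weeks in section 8.2.1 and the group sizes in section 6.1 (130 in A, 260 in B). The recall lengths are assumptions.

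**Scheduled adverse-event contacts after baseline.** A: weeks 12 and 24, so 2. B: weeks 4, 12 and 24, so 3. 3/2 = 1.5. This is a count of contacts, not an effect size.

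**Follow-up time covered by recall.** Suppose a patient reports events from the last w weeks before each visit, and no further back than the previous visit. The gaps between visits are 12 and 12 weeks in A, and 4, 8 and 12 weeks in B. Covered weeks out of 24:

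- A = 2 × min(w, 12)
- B = min(w, 4) + min(w, 8) + min(w, 12)

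Within weeks 0 to 4 alone, B covers min(w, 4) weeks and A covers max(0, w − 8).

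| Assumed look-back w (weeks) | A, of 24 | B, of 24 | Ratio B/A | Weeks 0–4 covered, A | Weeks 0–4 covered, B |
|---|---|---|---|---|---|
| 2 | 2 + 2 = 4 | 2 + 2 + 2 = 6 | 1.5 | 0 | 2 |
| 4 | 4 + 4 = 8 | 4 + 4 + 4 = 12 | 1.5 | 0 | 4 |
| 8 | 8 + 8 = 16 | 4 + 8 + 8 = 20 | 1.25 | 0 | 4 |
| 12 | 12 + 12 = 24 | 4 + 8 + 12 = 24 | 1.0 | 4 | 4 |

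With equal true rates and events spread evenly over follow-up, the ratio column is the apparent excess in B. It disappears when recall is perfect over 12 weeks. The last two columns show where the difference sits: with a look-back of 8 weeks or less, the scheduled visits reach none of weeks 0 to 4 in A.

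**GEEMA item on full days missed.** At week 12 the look-back is 12 − 4 = 8 weeks in B and 12 − 0 = 12 weeks in A. If both arms miss r days per week, A reports 12r and B reports 8r, a ratio of 12/8 = 1.5. At week 24 it is 24 − 12 = 12 weeks in both arms, ratio 1.0. Dividing by the weeks of look-back gives r in both arms at either visit. This needs no assumption about recall.

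**The case against.** The strongest reply has four parts.

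*Recording is not confined to scheduled visits.* Section 9.1 requires all adverse events in the CRF, section 11.1.1 tells patients to report events, and the week-12 question in A also covers weeks 0 to 4. This stands in part. What A loses is only what is forgotten or not volunteered, so the ratio can be as low as 1.0. It does not make ascertainment equal.

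*The analysis plan may deal with it.* Section 12.4 leaves detail to that plan and makes the secondary analyses descriptive, so silence in section 12 about common visits is no fault. That is right, and the point does not rest on it. The protocol itself fixes the collection, and no analysis plan can supply control-arm answers that were never sought. A descriptive side-by-side table has the same imbalance as a test.

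*The extra check in B is a reasonable safeguard after a switch.* Accepted; nothing here argues against it.

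*Most other outcomes are untouched.* A reader might infer that the virological, satisfaction, adherence and quality-of-life comparisons are all biased by the extra visit. The documents do not support that:

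- The virological endpoints are read at week 24, which both arms attend: "A viral load >500 copies/mL of viral RNA (HIV-1) confirmed at study week 24 will be considered as virological failure". The proportion below 50 copies/mL is also taken then.
- The withdrawal rule in section 7.2, "Patients who meet therapeutic failure criteria will be withdrawn from the study", is not tied to week 24, so a week-4 rebound can be found on schedule only in B. But this rule is not a listed endpoint. Early detection can lead to withdrawal or to reinduction, so its indirect effect on week-24 results has no clear direction.
- The CESTA and CD4 changes run from baseline to week 24. The adherence scale and the past-week GEEMA item have fixed look-backs.
- MOS-HIV and EQ-5D are not given at week 4. The only route to the primary endpoint is indirect: a patient withdrawn after a week-4 finding contributes a discontinuation-visit value.

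**Conclusion.** The point holds for non-serious adverse events and for one GEEMA item at week 12. For adverse events, the unequal questioning is certain from the schedule, but its effect is not. Under the assumed look-backs it inflates B relative to A by a factor of about 1.0 to 1.5. This assumes equal true rates, events spread evenly over 24 weeks, a sharp recall limit and no spontaneous reporting. Events clustered in the first four weeks would be affected more, and spontaneous reporting in A would reduce the effect. For the GEEMA item, the factor of 1.5 against A at week 12 follows from the visit dates alone. It matters because the adherence endpoint in sections 8.1.2 and 12.3 has no stated time point.

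Serious events, the week-24 endpoints and the primary comparison are not directly affected. This is an avoidable weakness in a secondary comparison that is cheap to repair, not a threat to the main result.

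**What to change.** 1. Add to sections 8.2.1 and 8.2.3 a scripted week-4 telephone adverse-event query for group A, with the same questions as the group B visit. Cost: about 130 short calls. The week-4 safety check in group B stays as it is.
2. State in section 12.3 or 12.4 that the GEEMA item on full days missed is compared between arms at week 24 only, or per week of look-back. Cost: one sentence.
3. Do not equalise the arms by dropping group B events first recorded at week 4 from the comparative table. Early events recalled at week 12 in A would stay in while those caught at week 4 in B went out, and a B patient who has already reported an event may not repeat it at week 12. That would understate group B toxicity.
4. If the call is not added, show the adverse-event comparison both with and without events first recorded at week 4, and state the unequal ascertainment beside it. This costs one extra table and shows the sensitivity, but does not recover the missing control-arm reports.

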## **8.2.2 Subject recruitment and treatment assignment**

The investigator is responsible for ensuring that each subject is eligible for the study before recruitment. Once a subject number has been assigned, it cannot be assigned to another subject.

## **8.2.3 Treatment assessments**

### **Quality of life measurement:**

Handling of questionnaires will be specifically detailed in Annex 2. As a general rule, each questionnaire should be provided to the patient based on the following premises:

- The following questionnaires ask patients about many aspects of their health state and health care. Questionnaires should be provided to patients before the physical examination, preferably in a quiet environment (e.g. the examination room or other room).
- It is important to be familiar with the content and format of questionnaires before they are given to the study participants. At the first visit, instruct the patient as follows:

"We would like you to answer some questions about how you feel and what you are able to do. Your answers will help us understand the effects of the medication you are taking. We would appreciate it if you would complete these questionnaires."

- You should then briefly explain the format of questions and how to complete them. The patient must complete the questionnaires before the clinical history and physical examination are made and the vital signs are measured.
- Questionnaires are very short and should take no more than 15-30 minutes to be completed. Before questionnaires are given to the patient, fill in the heading and DETACH THE PAGE for the investigator, which is adequately marked.

- Collect the completed questionnaires before the physical examination. Before continuing, review the questionnaires for potential omissions. If the participant has not answered any question, point this to him/her and have him/her complete the omissions.

### **Other study procedures:**

In addition to quality of life measurements (section 8.2), that will be done using the corresponding questionnaires, the following procedures will be performed to cover the secondary objectives of the study.

### **Screening visit:**

The eligibility of each subject will be established within 3 weeks of study randomization. This should be done at this visit, and the following should be documented:

- Written informed consent.
- Clinical history including a history of events related to the disease and drugs used in the previous 30 days.
- Physical examination (vital signs, height and weight).
- Urine pregnancy test (women of childbearing age).
- Complete blood count (red blood cell count, white blood cell count and differential, and platelet count).
- Fasting chemistry profile (alkaline phosphatase, ALT, AST, GGT, total bilirubin, creatinine, glucose, potassium, sodium, uric acid, and lipid profile (total cholesterol, HDL-C, LDL-C, VLDL-C, triglycerides).
- CD4 cell count
- HIV-1 RNA in plasma

### **Baseline visit:**

If laboratory data for confirming screening criteria have been obtained within two months of study recruitment and are available, the screening visit may be the same as the baseline visit.

The study drugs should start to be taken within 24 hours of the baseline visit. The following assessments should be available at the baseline visit:

- Physical examination (vital signs, height and weight).
- Quality of life questionnaires (MOS-HIV and EQ-5D)
- A negative urine pregnancy test for women of childbearing age.

- Complete blood count (red blood cell count, white blood cell count and differential, and platelet count).
- Fasting chemistry profile (alkaline phosphatase, ALT, AST, GGT, total bilirubin, creatinine, glucose, potassium, sodium, uric acid, lipid profile (total cholesterol, HDL-C, LDL-C, VLDL-C, triglycerides).
- CD4 cell count
- HIV-1 RNA in plasma: This will be measured in real time at the site using the standard virological methods at each site. The same methods should be used throughout the study for each subject.
- CESTA questionnaire to assess satisfaction with antiretroviral treatment.
- GEEMA questionnaire to assess treatment adherence
- VAS to assess treatment adherence
- Recording of concomitant medication
- Adverse events

Once the baseline visit procedures and assessments are reviewed, subjects will be centrally randomized at the study data center after data are received.

Patients randomized to group B will return for HIV RNA monitoring at treatment week 4 (+/- 2 days)

The following assessments should be completed at the **week 12 and week 24 visits or at the study discontinuation visit**. Study visits should be scheduled to occur within  $\pm 1$  week of the date specified for weeks 12 and 24, calculating the dates from the baseline visit:

- Physical examination (vital signs, weight).
- Complete blood count (red blood cell count, white blood cell count and differential, and platelet count)
- Fasting chemistry profile (alkaline phosphatase, ALT, AST, GGT, total bilirubin, creatinine, glucose, potassium, sodium, uric acid, lipid profile (total cholesterol, HDL-C, LDL-C, VLDL-C, triglycerides)
- CD4 cell count
- HIV-1 RNA in plasma: If the patient shows at any time a detectable viral load (> 50 copies/mL), the test should be repeated within 2 weeks for confirmation. Annex 1 provides suggestions for management of these cases
- Concomitant medication
- Adverse events

The following assessments should be completed at the end of the **week 12 and week 24 visits or at the early study discontinuation visit**.

- Questionnaires for assessing treatment adherence (GEEMA and VAS)
- Questionnaire for assessing treatment satisfaction (CESTA)
- Concomitant medication
- Adverse events

The following assessments should be completed at the end of the **baseline and week 24 visits or at the early study discontinuation visit**.

- Quality of life questionnaires (MOS-HIV and EQ-5D)
- Questionnaires for assessing treatment adherence (GEEMA and VAS)
- Questionnaire for assessing treatment satisfaction (CESTA)
- Concomitant medication
- Adverse events

